Patients undergoing abdominal surgery are more likely to develop AKI than those undergoing other noncardiac, nonvascular surgeries [12, 18]. Pneumoperitoneum is necessary for better visualization and manipulation in laparoscopic surgery. The increased intra-abdominal pressure (IAP) induced by pneumoperitoneum can activate the renin-angiotensin-aldosterone system (RAAS) and cause renal vascular and parenchymal compression [19], which will further undermine renal perfusion and create ischemic insults [20]. Prior literature has demonstrated the association between increased IAP and AKI in critically ill patients after abdominal surgery [21, 22]. Intraoperative oliguria and diminished glomerular filtration rates have also been observed [23]. These changes deteriorate with increases in pressure and extended durations [23]. However, several studies have reported conflicting results, indicating that laparoscopic surgery does not carry an additional risk of postoperative AKI [24–26]. Therefore, high-quality evidence is needed for a better understanding.

Low-pressure pneumoperitoneum (LPP, 7–10 mmHg) is recommended to minimize the ischemic organ injury caused by standard-pressure pneumoperitoneum (SPP, 12–15 mmHg) [27]. LPP has been successfully used in a series of abdominal and pelvic surgeries, such as laparoscopic hysterectomy, cholecystectomy, and adrenalectomy [28–31]. However, LPP compromises the working space and surgical field, leading to prolonged surgical durations [32]. Fortunately, studies have shown that deep neuromuscular blockade (NMB) can ameliorate this issue [33, 34] and facilitate the use of LPP [35–37]. However, such effects are still controversial [38, 39]; thus, further studies are still required.

Therefore, the objective of this study is to assess the effect of LPP *versus* SPP on renal function protection in patients with diabetes undergoing laparoscopic pelvic surgery and to evaluate whether deep NMB can improve surgical conditions compared with moderate NMB. We hypothesize that the use of LPP, facilitated by deep NMB, can improve postoperative renal function after laparoscopic pelvic surgeries.

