### Sample size calculation and statistical analysis

A previous study [15] reported that the standard deviation of serum CysC level after laparoscopic procedures is 0.738 ± 0.186 mg/dl. For a CysC difference of 0.05 mg/dl to be considered clinically significant, a power analysis program (G* power 3.1) calculated that a total sample size of 582 patients is needed to achieve 90% power at the 5% significance level. Considering a 10% dropout rate, a total of 648 patients (162 per group) is necessary. Approximately 5000 patients are scheduled for elective major pelvic surgery in PUMCH every year, and approximately 15% of them have diabetes; thus, one year is estimated as necessary to achieve adequate participant enrollment.

We will first compare the two SPP groups with the two LPP groups and then compare the two deep-NMB groups with the two moderate-NMB groups. Finally, all four groups will be compared.

The baseline characteristics and intraoperative factors of the enrolled patients will be evaluated using descriptive analysis. Continuous variables will be summarized as the mean  ±  standard deviation (SD) or median (interquartile range, IQR) as appropriate, whereas categorial variables will be summarized as the number (percentage). The baseline characteristics will be compared between groups using the standardized difference, and a standardized difference < 0.2 will be considered an acceptable balance between groups. Unbalanced variables at baseline will be included in the ANOVA or mixed-effects model to adjust for the potential confounding effect.

Considering the multiple measures of CysC, Cr, surgical condition rating scale, and renal tissue oxygen saturation at different time points, the effect of intervention in the whole timeframe will be analyzed by a mixed-effects model. Other continuous variables will be compared by two-sided independent Student’s t tests or the Mann–Whitney U test, as appropriate. Categorical variables will be analyzed by a Chi-square test or Fisher’s exact test, as appropriate. The Bonferroni method will be used to correct the potential increase in the probability of a type I error when analyzing the differences between the four groups.

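### Four of the seven secondary outcomes are compared on pooled factorial margins with tests that leave out the other randomized factor; precision is lost wherever that factor acts, and the stated covariate adjustment has no model to enter

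*Protocol article*

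**What the plan says.** The section on sample size and statistical analysis sets the order of comparison: "We will first compare the two SPP groups with the two LPP groups and then compare the two deep-NMB groups with the two moderate-NMB groups". A comparison of all four groups follows, with a Bonferroni correction.

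The methods are then allocated by type of outcome:

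- A mixed-effects model goes to the repeated measures: "Considering the multiple measures of CysC, Cr, surgical condition rating scale, and renal tissue oxygen saturation at different time points". That covers the primary outcome and three of the seven secondary outcomes in Table 3.
- For the rest, "Other continuous variables will be compared by two-sided independent" t tests or the Mann–Whitney test are named. In Table 3 this means intraoperative urine output and duration of surgery.
- "Categorical variables will be analyzed by a Chi-square test or Fisher’s exact test, as appropriate". In Table 3 this means urinary erythrocytes (postoperative days 1 and 3) and bucking or body movement.

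The paragraph before states the covariate rule: "Unbalanced variables at baseline will be included in the ANOVA or mixed-effects model". Variables count as acceptably balanced when the standardized difference is below 0.2. No sentence assigns an ANOVA to any outcome.

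**The concern.** In a balanced 2 × 2 design, each pooled margin is a fixed half-and-half mix of the two levels of the other factor. A two-sample test on that margin estimates its error from the total spread, which includes the gap between those two levels. Randomization fixes the mix equally in both margins, so the gap does not add to the sampling variability of the difference. Counting it as error makes the standard error larger than it should be.

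The article gives grounds to expect such a gap for three of the four outcomes:

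- **Duration.** The Background says that "LPP compromises the working space and surgical field, leading to prolonged surgical durations", and that deep block may ease the problem.
- **Bucking or movement.** The rating scale in Table 2 ties coughing and movement to inadequate relaxation, which bears on the pressure comparison.
- **Urine output.** The Background links raised abdominal pressure to intraoperative oliguria, which bears on the NMB comparison.

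Duration and bucking or movement are also two of the three outcomes chosen to judge surgical conditions, which is the stated purpose of the NMB comparison.

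The second problem needs no assumption about effects. The covariate rule names two models. One is assigned only to the repeated measures and the other to nothing. If a baseline variable is unbalanced, the analyst must either drop the rule for these four outcomes or choose a model after seeing the imbalance.

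**Working it through.** **1. The plan's own figure.** Inputs from the sample size paragraph: difference 0.05 mg/dl, SD 0.186 mg/dl, two-sided 5%, 90% power. The normal approximation gives 291 per margin, 582 in total. Allowing for 10% dropout, 582/0.9 = 646.7, so 647, and 648 as a multiple of four. Both stated totals reproduce, on a two-margin, two-sample basis.

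**2. Continuous outcomes.** Let σ be the within-cell SD and dσ the other factor's effect, with equal cells and additive effects. A half-and-half mix of two means dσ apart adds (dσ/2)² to the variance, so the t test uses σ²(1 + d²/4). The true sampling variance of the difference still rests on σ². With r = √(1 + d²/4):

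- actual type I error = 2[1 − Φ(1.96r)];
- power = Φ(δ − 1.96r), where δ = 1.960 + 0.842 = 2.802 gives the two-factor model 80% power;
- equivalent loss of patients = 648 × [1 − ((1.960 + δ − 1.96r)/δ)²].

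The documents give no d for any of these outcomes, so a range is shown. The value 0.269 is only the trial's design effect for cystatin C, 0.05/0.186, as a point of reference.

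| d (assumed) | Variance inflation | SE ratio r | Actual alpha | Power (80% with both factors) | Equivalent patients of 648 |
|---|---|---|---|---|---|
| 0 | 1.000 | 1.000 | 5.0% | 80.0% | 0 |
| 0.269 | 1.018 | 1.009 | 4.8% | 79.5% | 8 |
| 0.5 | 1.063 | 1.031 | 4.3% | 78.3% | 28 |
| 1.0 | 1.250 | 1.118 | 2.8% | 72.9% | 103 |

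Worked line for d = 1.0: r = √1.25 = 1.118; 1.96 × 1.118 = 2.191; 2.802 − 2.191 = 0.610; Φ(0.610) = 0.729; (2.570/2.802)² = 0.842; 648 × 0.158 = 103.

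Simulation of the pooled t test with 162 per cell and 10,000 runs gave type I error of 4.9%, 4.7%, 4.5% and 2.5% at d = 0, 0.269, 0.5 and 1.0, and the same SE ratios. The formulas are for the t test; the Mann–Whitney test was not computed.

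**3. Binary outcomes.** The pooled test uses p̄(1 − p̄). The variance that matters is the mean of p(1 − p) within the two levels of the other factor. All rates below are assumed.

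| Rates at the other factor's two levels | Pooled / within | SE ratio | Actual alpha |
|---|---|---|---|
| 10% and 10% | 0.0900 / 0.0900 | 1.000 | 5.0% |
| 5% and 15% | 0.0900 / 0.0875 | 1.014 | 4.7% |
| 10% and 30% | 0.1600 / 0.1500 | 1.033 | 4.3% |
| 10% and 50% | 0.2100 / 0.1700 | 1.111 | 2.9% |

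**4. The covariate rule.** Set the two sentences side by side. The rule needs an ANOVA or a mixed-effects model. The allocation of methods gives these four outcomes a t, Mann–Whitney, chi-square or Fisher test. None of those takes a covariate.

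**The case against.** **The loss may be trivial.** No effect size is documented. At the trial's own design effect the standard error is 0.9% too large, and at half an SD 3.1%. The tests are valid for the comparisons named, they err on the conservative side, the estimates are unbiased, and no power is claimed for these outcomes. All of this stands and sets the weight of the point.

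**Stronger readings that the documents do not support:**

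- *That intervals are too wide for all four outcomes, whatever happens.* The excess needs a non-zero effect of the other factor. Nothing in the article says that NMB depth changes urine output or urinary erythrocytes, and the section on adverse events says there is no evidence of renal toxicity from the deep-block dosage in patients without end-stage renal disease. So the pressure comparison for those two outcomes has no documented loss. The Background also calls the benefit of deep block controversial.
- *That the loss equals 38 patients at d = 0.5 and 130 at d = 1.0*, from 648 × [1 − 1/(1 + d²/4)]. That treats the extra variance as real sampling error. It describes interval width; for power the losses are 28 and 103.
- *That bias or excess false positives follow.* Neither does.

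**Interaction.** Deep block easing a problem caused by low pressure describes an interaction, whereas 1 + d²/4 assumes additive effects. If NMB acted only under low pressure, with effect d there, inflation in the pressure comparison would be 1 + d²/8, or 12.5% of variance at d = 1.0 instead of 25%. The loss is smaller but still present.

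**The covariate rule.** The mention of ANOVA may mean that a linear model was intended for the continuous outcomes, and the sentence does not expressly promise adjustment of the chi-square outcomes. The rule would also seldom fire on the margins. With 324 per side the standard error of a standardized difference is √(2/324) = 0.079, so chance imbalance beyond 0.2 has probability about 1.1% per variable. Between two single groups of 162 it is √(2/162) = 0.111, and about 7%. A full analysis plan could settle this, but the article does state which tests apply, and they do not fit the rule beside them.

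**Conclusion.** The point holds as a limited one on secondary outcomes. The stated tests leave out a factor that the trial itself randomizes. Where that factor acts, precision is lost for no gain: nothing at d = 0, about 3% of the standard error and two points of power at d = 0.5, and about 12% and seven points at d = 1.0. These figures rest on assumed d, equal cells, additive effects and a starting power of 80%. The protocol gives grounds for such an effect for duration, for bucking or movement, and for urine output in the NMB comparison only.

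Separately, and without any assumption about effects, the covariate rule points to an ANOVA that no outcome is assigned, while the tests named for these four outcomes cannot adjust. The primary analysis uses a mixed-effects model and is untouched.

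**What to change.** Reword the two sentences that name the tests:

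- **Urine output and duration of surgery:** one linear model (two-way ANOVA or ANCOVA) with pressure and NMB depth both as terms, reporting the mean difference that Table 3 asks for. If the data are skewed, use robust standard errors, which keep that mean difference, or a log scale, which turns it into a ratio.
- **Urinary erythrocytes (each day) and bucking or movement:** a Mantel–Haenszel test and risk difference stratified by the other factor, or logistic regression with both factors. The risk difference matches the difference in proportions in Table 3.
- **Covariates:** say that any baseline variable the plan calls for enters these same models. For the binary outcomes that means the logistic version.

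The cost is the rewording. No new data or patients are needed, and if the other factor has no effect, essentially nothing is given up.

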### Outcome measures

The primary outcome is serum CysC level, which is a sensitive biomarker of renal injury, and this will be measured 30 min before pneumoperitoneum insufflation (T1), 30 min after pneumoperitoneum deflation (T2), 24 h postoperatively (T3), and 72 h postoperatively (T4). Among them, T1 will be the baseline. The mean difference of the serum CysC between groups will be used as the effect measure. We will compare the serum CysC between groups throughout T2, T3, and T4, using mixed-effect model which can provide an estimate for the overall effect in the whole timeframe.

The secondary outcomes include four indicators of renal function: (1) serum Cr level measured at T1, T2, T3, and T4; (2) intraoperative urine output; (3) the presence of erythrocytes in urinary sediment on postoperative days 1 and 3; and (4) renal tissue oxygen saturation measured every 15 min following pneumoperitoneum insufflation, and cerebral oxygen saturation will be used as an internal reference to adjust individualized differences. The other three secondary outcomes selected to evaluate surgical conditions are (1) surgical condition rating scale measured every 15 min starting from the introduction of the first trocar by five surgeons independently, (2) duration of surgery, and (3) the occurrence of bucking or body movement during the surgery. The details of the secondary outcomes are demonstrated in Table 3.

**Table 3 Tab3:** The secondary outcomes

Domain	Measurement	Metric	Aggregation	Time point
renal function	serum Cr level	difference between groups in the whole timeframe	mean	30 min before PP insufflation, 30 min after PP deflation, postoperative 24 h, and postoperative 72 h
renal function	intraoperative urine output	difference between groups	mean	NA
renal function	the presence of erythrocytes in urinary sediment	difference between groups	portion	postoperative day 1 and day 3
renal function	renal tissue oxygen saturation	difference between groups in the whole timeframe	mean	every 15 min since PP insufflation
surgical condition	surgical condition rating scale	difference between groups in the whole timeframe	median	every 15 min starting from the introduction of the first trocar
surgical condition	duration of surgery	difference between groups	mean	NA
surgical condition	the occurrence of bucking or body movement during surgery	difference between groups	portion	NA

*Abbreviations*: *NA* not applicable, *PP* pneumoperitoneum

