We will also investigate the interaction between pneumoperitoneum pressure and NMB on postoperative renal function. The difference in serum Cysc levels at T2 between the S + D and L + D groups will be compared with that between the S + M and L + M groups. If there is no significant difference, we will assume there is no interaction.

We will perform statistical analysis using R (version 3.4.4). Two-sided *P* values < 0.05 will be considered significant.

Based on ITT principle, we will analyze all the post-randomization cases, including the ones with missing data. The missing data of the repeatedly measured outcomes will be imputed using the “last observation carried forward” method, while the missing data of other outcomes will be imputed by baseline data. Sensitivity analysis will be performed to assess the bias that may be introduced due to nonadherence to protocol or missing data.

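### The pressure-by-NMB interaction is tested at T2 only, and a non-significant result is taken to mean no interaction, with about 37% power for an interaction the size of the target effect

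*Protocol article*

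**What the plan says.** Four places in the protocol article bear on the point.

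- **Study design** assumes that the two interventions do not interact on the primary outcome.
- **Outcome measures** defines the primary comparison of serum cystatin C as a mixed-effects analysis across T2, T3 and T4, "which can provide an estimate for the overall effect in the whole timeframe".
- **Sample size calculation and statistical analysis** sets the order of comparisons: the two standard-pressure groups against the two low-pressure groups, then deep against moderate NMB, then all four groups with a Bonferroni correction.
- **The same section** describes the interaction check. It begins "The difference in serum Cysc levels at T2 between the" and contrasts S + D versus L + D with S + M versus L + M. The rule that follows is "If there is no significant difference, we will assume there is no interaction".

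The sample size is set for a pooled difference of 0.05 mg/dl. No power is given for the interaction.

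**The concern.** There are two separate problems.

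**Time point.** The check uses one of the three post-baseline measurements that make up the primary effect. A null result at T2 says nothing direct about 24 h and 72 h, although the stated interest is postoperative renal function.

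**Inference.** The rule turns P > 0.05 into a working conclusion of absence. In a balanced 2 × 2 trial sized for its main effects, the interaction is estimated with twice the standard error. A non-significant result is then likely even when the effect of pressure differs between depths by as much as the trial's own target.

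The question is not remote in this trial. The Background states: "We hypothesize that the use of LPP, facilitated by deep NMB, can improve postoperative renal function after laparoscopic pelvic surgeries". Readers will want to know whether low pressure works equally well at both depths. Under the rule, a real difference between depths of the target size would more often than not be reported as no interaction, and the pooled figure would be taken to apply to both depths.

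**Working it through.** **Inputs, all from Sample size calculation and statistical analysis**
- Target difference 0.05 mg/dl: "For a CysC difference of 0.05 mg/dl to be considered clinically significant".
- SD 0.186 mg/dl: "the standard deviation of serum CysC level after laparoscopic procedures is 0.738 ± 0.186 mg/dl", read as mean 0.738 and SD 0.186.
- Evaluable total, power and alpha: "a total sample size of 582 patients is needed to achieve 90% power at the 5% significance level".
- Two-sided testing: P "values < 0.05 will be considered significant".
- Balanced allocation to four groups, so 582/4 = 145.5 evaluable per cell. As randomized, 648/4 = 162 per cell.

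**Step 1. Reproduce the plan's figure**

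n per pooled arm = 2 × (1.960 + 1.282)² × 0.186² / 0.05² = 290.8, rounded up to 291. The total is 582, as stated. This confirms both the reading of the SD and that the trial is sized for a main effect.

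**Step 2. Standard errors at 582**
- Main effect (291 vs 291): 0.186 × √(2/291) = 0.0154.
- Interaction (difference of two differences, four cells): 0.186 × √(4/145.5) = 0.0308, exactly twice as large.

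**Step 3. Power of the interaction test, two-sided 5%**

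Power ≈ Φ(δ/SE − 1.96), plus the far tail where it matters. For δ = 0.05: 0.05/0.0308 = 1.62, and Φ(1.62 − 1.96) = 0.37.

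| True interaction (mg/dl) | Power, N = 582 | Power, N = 648 (SE 0.0292) |
|---|---|---|
| 0.025 | 13% | 14% |
| 0.05 | 37% | 40% |
| 0.075 | 68% | 73% |
| 0.10 | 90% | 93% |

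At 582, 90% power is reached only at 0.10, twice the target difference.

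**Step 4. What a non-significant result leaves open**

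The 95% half-width is 1.96 × 0.0308 = 0.060 at 582 and 1.96 × 0.0292 = 0.057 at 648. A non-significant estimate lies within one half-width of zero, and both half-widths exceed 0.05. At these standard errors, every non-significant result therefore has an interval that contains +0.05 or −0.05. An estimate of exactly zero gives −0.060 to +0.060.

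**Step 5. An example**

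Suppose low pressure lowers cystatin C by 0.05 at one NMB depth and by 0 at the other. The interaction is 0.05 and the pooled effect is (0.05 + 0)/2 = 0.025. The rule would lead to an assumption of no interaction in about 1 − 0.37 = 63% of such trials.

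**Step 6. Sensitivity to baseline adjustment**

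The interaction test is described without adjustment for T1. If T1 were a covariate, the SE would be multiplied by √(1 − ρ²). The documents give no T1–T2 correlation ρ, so these values are assumptions. At 582, power for 0.05 would be 46% at ρ = 0.5, 62% at 0.7 and 77% at 0.8. The half-width would be 0.060 × 0.866 = 0.052 at ρ = 0.5 and 0.060 × 0.714 = 0.043 at ρ = 0.7. The statement in Step 4 about every non-significant result therefore holds for the unadjusted test, but not under strong baseline correlation.

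**The case against.** The strongest reply is that little hangs on this test. The pooled comparisons and the four-group comparison are laid down unconditionally, and no analysis is switched on or off by the interaction result. A reader might infer that the test gates the primary analysis, or that an undetected interaction would invalidate the pooled estimate. The documents support neither. With balanced randomization to four groups, the pooled pressure effect is an unbiased average over the two depths with or without interaction, and its standard error and type I error do not depend on this test. That reply stands, and it limits the point to interpretation.

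Other replies stand in part:

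- **Low interaction power is generic.** It comes with any 2 × 2 trial sized for main effects and is not itself a fault. The fault is the conclusion drawn from non-significance.
- **The four-group comparison may show the pressure effect at each depth.** The article does not list its contrasts, and comparing cells does not test whether the two effects differ. It mitigates the problem but does not undo the rule.
- **The protocol says it will assume, not that it has proved.** A reader might take the sentence as a claim of proof, which is too strong. It still makes P > 0.05 sufficient for treating interaction as absent.
- **The rationale does not predict an interaction on cystatin C.** A reader might infer that it does from the phrase about facilitation. The Background has deep NMB helping mainly through the surgical view, its objective links pressure to renal function and NMB to surgical conditions, and Study design assumes no interaction. An interaction on cystatin C is plausible, but not stated.
- **T2 may be informative.** The article presents cystatin C as an early marker and gives no time course, so it cannot be said that an effect would be invisible at T2. The mismatch with the T2–T4 effect remains.

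**Conclusion.** The point holds as a fault in a stated rule. The interaction is examined at a time point that does not match the primary effect, and non-significance is given a meaning it cannot carry. From the protocol's own inputs, power is about 37% for an interaction of 0.05 mg/dl (about 40% with all 648 analysed), and the 95% half-width is about 0.060.

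These figures assume SD 0.186 at T2, equal cells, and no adjustment for T1. Adjustment would raise the power by an amount the documents do not allow one to fix.

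The consequence is confined to one claim, that the pressure effect is the same at deep and moderate NMB. The primary pooled result is unaffected.

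**What to change.** 1. Delete the sentence that assumes no interaction after a non-significant test.
2. Estimate the pressure × NMB term in the same T2–T4 mixed model as the primary outcome, in place of the comparison at T2 alone, and report it with its 95% confidence interval.
3. Report the low- versus standard-pressure effect within deep NMB and within moderate NMB, each with its interval, beside the pooled effect and whatever the interaction P value.

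The change should be made before the allocation is unblinded. It costs some wording and a few extra lines of output, with no new data. A larger sample is not asked for: 90% power for an interaction of 0.05 would take about 2,327 evaluable patients, roughly four times 582. The price is a less definite statement about interaction, which is what the design can support.

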### Data collection

The following demographic data and previous medical history will be collected by a data collector preoperatively from the medical records: sex, age, height, weight, duration of diabetes, and the presence of any complications of diabetes.

Peripheral venous blood samples will be extracted at T1, T2, T3, and T4, and urine samples will be obtained on the morning of postoperative days 1 and 3. The samples will be sent immediately to the clinical laboratory in PUMCH and will be analyzed by the staff there. Blood samples will be centrifuged at room temperature to obtain serum. Serum CysC concentration will be determined by sandwich enzyme-linked immunosorbent assay (ELISA), and Cr will be measured using an enzymatic method. Urine samples will be analyzed by automated urine microscopy analysis. All the samples will be handled within one hour since their arrival at the laboratory. We do not plan to store the samples after the study.

During the surgery, in addition to the secondary outcomes, two data collectors will record the heart rate, ABP, SV, and SVV every 15 min. They will also record the amount of crystalloid and colloid infused, the amount of transfusions, and the estimated blood loss.

There is an anesthesiologist and a surgeon in charge of monitoring the adherence to the protocol. Any suspected nonadherence during participant recruitment, randomization, intervention, data collection, or outcome assessment will be recorded. Based on the intention-to-treat (ITT) principle, all the randomized participants will be analyzed, despite any nonadherence to the protocol.

Data will be collected in the paper-based case report form (CRF) and then entered into a digital database by two independent investigators. Each patient will be distinguished by a unique serial number, and his or her name will be concealed. The database will be secured by a password, which will be restricted to the Data Safety Monitoring Committee (DMC), which is composed of two anesthesiologists with more than 10 years of experience. They will check the completeness and accuracy of the data, and the auditing will be independent from that of the other investigators. The information recorded in medical charts and saved in monitors will be traced to correct and supplement the data. The database will be locked up after the entry of the last case. The allocation will not be unblinded until all data analysis is completed; thus, the data analyst will also be blinded.

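### Last observation carried forward ahead of a mixed model is unnecessary and can bias the cystatin C comparison, and the baseline-imputation rule cannot be carried out for the single-measure outcomes

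*Protocol article*

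**What the plan says.** All points are in the Protocol article.

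- **Repeated outcomes.** The section Sample size calculation and statistical analysis states: "The missing data of the repeatedly measured outcomes will be imputed using the" last-observation-carried-forward method. The same section treats four outcomes as repeated: CysC, creatinine, the surgical condition rating scale and renal tissue oxygen saturation. For these, "the effect of intervention in the whole timeframe will be analyzed by a mixed-effects model".
- **All other outcomes.** The rule continues: "while the missing data of other outcomes will be imputed by baseline data".
- **Sensitivity analysis.** "Sensitivity analysis will be performed to assess the bias that may be introduced due to nonadherence to protocol or missing data". No method is given.
- **Primary outcome schedule (Outcome measures).** CysC is taken 30 min before insufflation (T1), then "30 min after pneumoperitoneum deflation (T2), 24 h postoperatively (T3), and 72 h postoperatively (T4"). On T1: "Among them, T1 will be the baseline". The groups are compared over T2 to T4 "using mixed-effect model which can provide an estimate for the overall effect in the whole timeframe".
- **Urine (Data collection).** "urine samples will be obtained on the morning of postoperative days 1 and 3". The preoperative data listed there are demographics and diabetes history.

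**The concern.** There are two separate defects.

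**LOCF before a mixed model.** A likelihood-based mixed model uses every observed value of an incomplete series and is valid under missing at random. LOCF adds a stronger assumption, that nothing changes after the last sample, and then counts copied values as measurements. A patient lost after T2 is given the value from half an hour after deflation at both 24 h and 72 h. A patient with only T1 is given no change at all. The Background says creatinine may take 2 to 3 days to rise after renal ischaemia, so holding an early postoperative value constant fits poorly with the protocol's own account of how renal markers behave. The primary outcome falls under this rule, and the plan allows for 10% dropout.

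**Imputation from baseline.** The outcomes left to this rule arise during or after surgery. If no baseline value exists, the analyst has to invent a substitute, and the plan does not say which.

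**Working it through.** **1. The plan's own figure.** With a difference of 0.05, SD 0.186, two-sided 5% and 90% power, the normal approximation gives 291 per factorial margin, 582 in total. Allowing for 10% dropout, 582/0.9 = 646.7, so 647, and 648 for four equal groups. The stated figures reproduce. The number randomised per margin is 648/2 = 324, and 10% of 648 is about 65 patients.

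**2. Bias formula for loss after T2.** Let d_S and d_L be the proportions lost after T2 under standard and low pressure. Let g be the mean change from T2 to T3/T4 under standard pressure, and e the part of the treatment effect that appears only after T2. Loss is taken as unrelated to the CysC value. For the mean over T2 to T4, difference standard minus low,

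bias from LOCF = −(2/3) × [(d_S − d_L) × g + d_L × e].

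The bias is zero when loss is equal and e = 0. That covers both no effect and an effect constant over T2 to T4.

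**3. Standard error.** Assumed: correlation 0.7 between times, no baseline adjustment, patient means over T2 to T4 standing in for the mixed model.
- SD of a patient mean = 0.186 × √[(1 + 2 × 0.7)/3] = 0.1664.
- SE with complete data = 0.1664 × √(2/324) = 0.0131.
- Under LOCF a lost patient's three values are identical, so that patient's variance is 0.186². The SE rises to between 0.0133 and 0.0136 in the scenarios below.

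**4. Late effect.** Effect 0 at T2 and 0.05 at T3 and T4; 10% lost in each arm.
- True mean effect = (0 + 0.05 + 0.05)/3 = 0.0333. Power = Φ(0.0333/0.0131 − 1.96), about 72%.
- Bias = −(2/3) × 0.10 × 0.05 = −0.0033, so LOCF estimates 0.0300. Power = Φ(0.0300/0.0133 − 1.96), about 61 to 62%.
- In simulation, a likelihood analysis of the same incomplete data keeps the estimate at 0.033 and power at about 71 to 72%. Nearly all of the loss therefore comes from LOCF, not from the missing samples.

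**5. No effect, unequal loss.** 5% lost under standard pressure, 15% under low pressure.

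| Assumed common rise after T2 | False difference | Share of 0.05 | Type I error, closed form | Type I error, simulation |
|---|---|---|---|---|
| 0.10 | (2/3) × 0.10 × 0.10 = 0.0067 | 13% | 7.9% | about 7 to 8% |
| 0.20 | (2/3) × 0.10 × 0.20 = 0.0133 | 27% | 16.5% | about 15 to 16% |

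Reversing which arm loses more reverses the sign. The likelihood analysis gives no bias and about 5% in both rows.

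**6. Loss before T2.** If 10% in each arm have only T1, LOCF carries T1 forward and a constant effect of 0.05 becomes 0.9 × 0.05 = 0.045. By the plan's own two-mean formula with 324 per margin, power is 86.9%. Using only the roughly 291 per margin with data (0.9 × 324 = 291.6) gives 90.0%.

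**7. The baseline rule, outcome by outcome.**

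| Outcome outside the mixed model | Baseline value available? |
|---|---|
| Intraoperative urine output | Cannot exist |
| Duration of surgery | Cannot exist |
| Bucking or body movement | Cannot exist |
| Erythrocytes in urinary sediment | None described; urine is taken on postoperative days 1 and 3 |

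**The case against.** The strongest reply is that the harm is conditional and probably modest.

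- **Constant effect.** If the effect is 0.05 at T2, T3 and T4 and 10% in each arm are lost after T2, LOCF still estimates 0.050, with power near 97% either way. This stands.
- **Equal loss.** With no effect and equal loss there is no bias. At 8% versus 12% loss, type I error is only about 5 to 7%. This stands too.
- **Likelihood of unequal loss.** Patients stay at least 3 days, so the 72 h sample falls in or near the admission. Patients and staff are described as blinded, and the Discussion expects non-adherence to be equally likely in each group. This makes heavy unequal loss less likely, but that expectation is asserted rather than shown, and T4 sits close to the earliest discharge.
- **Few gaps in theatre data.** Urine output, duration and movement are recorded during surgery, and charts and monitors will be traced to fill gaps. The second rule may seldom be needed, and it concerns secondary outcomes only. It still cannot be applied when it is needed.
- **Erythrocytes.** Two samples might bring this outcome under LOCF, but a missing day 1 value then has nothing before it to carry. Table 1 is not shown, so a preoperative urine test cannot be excluded.
- **Planned sensitivity analysis.** It is promised, and its method may properly be left to the analysis plan. It softens the LOCF problem but leaves LOCF as the primary rule and does nothing for a rule without an input.

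**Conclusion.** Both rules are defective as written and should be changed before analysis. The LOCF rule is unnecessary before the planned model and can bias the primary comparison. In the scenarios above, the cost is about 10 points of power for a late effect, or a type I error of about 7 to 16% under 5% versus 15% loss with a common rise. The correlation, the CysC trajectory, the timing of the effect and the loss by arm are all assumptions. The document supplies only the SD, the target difference, the sample size and the overall 10% dropout. The baseline rule needs no simulation: three outcomes cannot have a baseline, and none is described for the fourth.

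A reader might infer more than this, and the document does not support it:
- That LOCF necessarily biases the CysC result or always shrinks it. Size and direction depend on the assumptions, and the bias can be zero.
- That CysC lacks a baseline. T1 is measured and named as the baseline; the missing baseline concerns only the non-repeated outcomes.
- That the loss should be taken from 291 per margin. That number is already net of the 10% dropout; 324 per margin are randomised.

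This should be fixed, but it does not by itself invalidate the primary analysis.

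**What to change.** 1. Delete both imputation rules.
2. Analyse CysC, creatinine, the rating scale and renal tissue oxygen saturation by the likelihood-based mixed model on all observed values, without imputation, each patient in the assigned arm.
3. Analyse urine output, duration of surgery, bucking or movement and urinary erythrocytes on observed values, and report the number missing by arm.
4. Keep the promised missing-data sensitivity analysis and give it a method. A delta-adjusted analysis of CysC at T3 and T4 is one suitable choice among several.

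The cost is a change of wording and slightly more programming, with no extra patients or samples. The price is that the primary analysis then relies on missing at random, which step 4 is there to test.
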